**Fig. 1 Fig1:**
[figure not shown]
Participant flow through the study from recruitment to study endpoint. ^1^been together ≥8 weeks, indicated/confirmed on phone that RSP likely to participate; ^2^refer to eligibility criteria; ^3^protocol violation means not in modified intention-to-treat (mITT) primary analysis or per protocol analysis; ^4^eligible for mITT and per protocol analyses if week 4 and/or 12 provided but with missing data, not eligible for safety analysis; ^5^if female participant does not attend clinic visits but does return a swab, eligible for secondary endpoints; ^6^if female attends at week 4 but not week 12, still be eligible for mITT; if no visits but returns a swab, eligible for secondary endpoints; if no visits or swabs, protocol violation. Abbreviations: LTFU, Loss to follow up; W, withdrawn

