### Intervention

All female participants will receive oral metronidazole 400 mg twice daily for 7 days, or if contraindicated, a 7-day regimen of topical vaginal 2% clindamycin cream.

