#### Intervention – concurrent male partner treatment

Male partners randomised to the *Intervention Group* will receive concurrent male partner treatment of combined oral metronidazole 400 mg BID and topical 2% clindamycin cream to be applied to the glans penis and upper shaft (under the foreskin if uncircumcised) BID for 7 days.

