#### Control – female treatment only (current standard of care)

Male partners randomised to the *Control Group* will not receive treatment and the control for the trial is the current standard of female treatment only. The twice daily application of a topical placebo for 7 days to the penile skin would be highly likely to influence bacterial composition/microbiota. Due to the concerns of this impact on the effect estimate a decision was made against providing a topical placebo to males randomised to the control group.

Adherence will be measured via questionnaire the day following antibiotic therapy (day 8). Participants can discontinue trial treatment and remain in the trial. They can also withdraw from the follow-up assessments at any time.

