### Statistical methods

Analysis and reporting of the trial will be in accordance with the Consolidated Standard of Reporting Trials (CONSORT) guidelines. A detailed Statistical Analysis Plan will be written close to final data lock, but before any analyses are performed, that will define all analyses in detail. Enrolment and longitudinal specimen and questionnaire data will be entered into two separate password-protected online databases within REDCap and then imported into a statistical package (Stata) for analysis.

The Primary Analysis is a mITT analysis. All randomised women will be analysed as randomised if they 1) returned for ≥1 clinical visit, 2) took one or more doses of antimicrobial therapy, and 3) are part of the evaluable population. Sensitivity analyses will include analyses that take into consideration adherence to treatment (for women and/or men). Women who attend at week 4 but not week 12, are still eligible for the primary outcome analysis. Primary analyses will be simple unadjusted two-group comparisons of the randomised arms using Cox regression. If there are important imbalances in baseline characteristics, further adjusted analyses will be performed. Cox regression analyses will be also used to assess co-variates associated with recurrence including demographics, sexual practices, contraception use, smoking and other factors previously shown to be associated with BV recurrence.

Secondary analyses include a per protocol analysis for participants qualifying for the mITT population and who adhered to ≥70% of doses of the medication(s) prescribed (i.e. ≥10 doses of a 14-dose prescription or ≥ 5 doses of a 7-dose prescription). Any AEs leading to cessation of treatment, and all reported clinical AEs will be summarised descriptively. This will include every male who took ≥1 dose of at least one of the investigational drugs.

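### Per-protocol entry requires at least 70% adherence, yet a missing male day-8 form appears not to exclude a couple; and if male doses count, the set is selected differently by arm

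*Protocol article*

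**What the plan says.** All of this is in the protocol article.

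- **Membership rule (Statistical methods).** One of the planned secondary analyses is "a per protocol analysis for participants qualifying for the mITT population and who adhered to ≥70% of doses of the medication(s) prescribed", with cut-offs of "≥10 doses of a 14-dose prescription or ≥ 5 doses of a 7-dose prescription". The modified intention-to-treat (mITT) set from which it is drawn is defined on women: "All randomised women will be analysed as randomised if they 1) returned for ≥1 clinical visit", with further conditions.
- **What is prescribed.** Women in both arms are given one product over 7 days, either oral metronidazole or, where that is contraindicated, vaginal clindamycin cream (section Intervention). Intervention men are given two: "concurrent male partner treatment of combined oral metronidazole 400 mg BID and topical 2% clindamycin cream". Control men "will not receive treatment and the control for the trial is the current standard of female treatment only".
- **Where adherence comes from.** The section on the control arm says "Adherence will be measured via questionnaire the day following antibiotic therapy (day 8"). The section on home and clinic follow-up likewise places adherence on the day-8 form. No other source is named.
- **What a missing form costs.** The Protocol deviation section says that a man who does not return the day-8 questionnaire loses the safety analysis. It names no other consequence. Note 4 to Fig. 1 describes participants who are "eligible for mITT and per protocol analyses if week 4 and/or 12 provided but with missing data, not eligible for safety analysis".
- **An exclusion in one arm only.** Item vi of the Protocol violation section removes a couple from both the mITT and per-protocol analyses if an intervention man uses no antibiotic. It has no control-arm counterpart.

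**The concern.** There are two linked problems.

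First, a set defined by at least 70% adherence cannot coherently include couples for whom the relevant adherence is unknown. If a missing male form leaves a couple eligible, the set contains an unknown share of men who may have taken few doses. Without the form, no stated source would even show whether item vi of the Protocol violation section applies.

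Second, if male doses count, the two arms are filtered on different behaviour. A control couple enters on the woman's doses; an intervention couple must also pass on the man's. Men who complete a week of treatment may also be those who follow the advice to abstain or who use condoms. The Sample size section itself cites a 50% risk reduction from consistent condom use. The filter could therefore keep lower-risk couples in one arm only, and the per-protocol hazard ratio could favour treatment without a drug effect. The two problems push in opposite directions, so the result would be hard to read.

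**Working it through.** **1. The plan's own cut-offs.** 10/14 = 71.4% and 5/7 = 71.4%; one dose fewer gives 9/14 = 64.3% and 4/7 = 57.1%. The cut-offs agree with the 70% rule. The threshold is not in question, only who must meet it and how a missing value is treated.

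**2. The rules side by side.**
- Statistical methods: entry needs at least 70% adherence.
- Adherence is recorded on the day-8 form.
- Protocol deviation: a missing male day-8 form costs the safety analysis.
- Fig. 1, note 4: some participants with missing data stay per-protocol eligible but lose the safety analysis.

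A missing male day-8 form is the event that the Protocol deviation section ties to losing the safety analysis, so note 4 most plausibly refers to it. Followed together, these rules admit couples with unknown male adherence.

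**3. Whose doses count.** The bracketed plural in the membership rule fits only intervention men, because women receive one product and control men none. Item vi also makes male non-use a reason for per-protocol exclusion. Both favour counting the man's doses, but no sentence says so.

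**4. Effect on the size of the set (assumed adherence).** Let a_w and a_m be the adherent fractions of women and men, taken as independent. The control arm keeps a_w and the intervention arm a_w × a_m. From the planned 145 evaluable couples per arm with a_w = 0.90, control keeps about 130. Intervention keeps 145 × 0.90 × a_m = 91, 104 or 117 for a_m = 0.7, 0.8 or 0.9. Power for 40% versus 24% (normal approximation, no continuity correction) is then 71%, 74% or 77%, against 83.5% at 145 per arm.

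**5. Selection with no drug effect (assumed inputs).** Let a be the adherent fraction of intervention men, r the recurrence risk in partners of adherent men relative to partners of non-adherent men, and b the risk in the latter group. With no drug effect the overall risk stays at the planned 0.40:

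a·r·b + (1 − a)·b = 0.40, so b = 0.40/(a·r + 1 − a)

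The intervention per-protocol risk is r·b. Against 0.40 in control, the risk ratio is r/(a·r + 1 − a).

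| a | r = 0.6 | r = 0.7 | r = 0.8 | r = 1 |
|---|---|---|---|---|
| 0.7 | 0.6/0.72 = 0.833 | 0.7/0.79 = 0.886 | 0.8/0.86 = 0.930 | 1 |
| 0.8 | 0.6/0.68 = 0.882 | 0.7/0.76 = 0.921 | 0.8/0.84 = 0.952 | 1 |
| 0.9 | 0.6/0.64 = 0.938 | 0.7/0.73 = 0.959 | 0.8/0.82 = 0.976 | 1 |

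The range is 0.83–0.98, and exactly 1 when male adherence is not prognostic.

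**6. Dilution from missing forms (assumed inputs).** Let m be the fraction of intervention men without a form and a the adherent fraction among those who return one. The share of the intervention per-protocol set with unknown male adherence is m/((1 − m)·a + m). For m = 0.10 and a = 0.8 this is 0.10/0.82 = 12%; for m = 0.20 and a = 0.7 it is 0.20/0.76 = 26%.

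Suppose half of these men did not adhere and their partners carry the full control risk. The non-adherent share is s = 0.5m/((1 − m)·a + m), and the risk is 0.24 + 0.16·s. For m = 0.10, a = 0.9: s = 0.05/0.91 = 0.055, risk 0.249, ratio 0.62. For m = 0.20, a = 0.7: s = 0.10/0.76 = 0.132, risk 0.261, ratio 0.65. A true ratio of 0.24/0.40 = 0.60 would thus appear as 0.62–0.65. Some benefit from partial dosing would make the dilution smaller.

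**The case against.** The strongest reply is that both problems rest on a couple-level rule the article never states. The mITT set is defined on women. If only the woman's doses count, the 70% filter is the same in both arms, a missing male form does not bear on it, and note 4 can stand beside the membership rule. This is a fair reading of part of the text, and a reader should not infer that a two-person 70% rule has been written. But it leaves the bracketed plural without a natural referent. Item vi would still exclude on male use in one arm only, and could not be checked from any stated source when the form is missing.

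A reader might also infer that unknown adherence is formally counted as at least 70%. The article does not say that. Note 4 mentions only missing data, its anchor is in a figure not shown, and the membership rule taken alone would exclude anyone not shown to have adhered. What stands is that the rules point in different directions.

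It can also be said that the statistical analysis plan is to define the analyses in detail, and that adherence sensitivity analyses for women and/or men are already foreseen. That would answer a complaint of missing detail. It does not remove an eligibility note that already sits badly with the set's definition.

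Finally, some asymmetry is inherent when only one arm treats the man. That is correct, and is why the result needs a label and a companion analysis rather than a new filter. Filtering on the woman alone would equalise the arms but ignore adherence to the only treatment that differs between them, so it is not a good replacement.

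**Conclusion.** The point holds in a limited form. Per-protocol membership is fixed inconsistently, subject to the inferred link between note 4 and the male day-8 form. Where male doses count, the set is selected differently by arm, and the contrast is open to bias if male adherence is prognostic.

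The sizes are illustrations. The article gives no adherence rate, no rate of missing forms and no figure for the prognostic value of male adherence. On the stated assumptions, selection alone gives a risk ratio of 0.83–0.98 with no drug effect, and missing forms move a true 0.60 to 0.62–0.65.

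It would be wrong to infer that the trial's main efficacy estimate is affected. The per-protocol analysis is secondary, and neither the primary mITT analysis nor the sample size uses the 70% rule. This is a minor point, worth settling before any analysis.

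**What to change.** 1. Reconcile Fig. 1 note 4 and the Protocol deviation section with the Statistical methods section. Per-protocol entry should require a returned day-8 form documenting at least 70% of doses for each person whose adherence counts, and the text should say whose adherence that is.
2. Label the per-protocol result as supportive and non-randomised.
3. Add a complier-average (instrumental-variable) estimate as a supplementary analysis, with randomisation as the instrument. In its simplest form it is the 12-week risk difference divided by the adherent fraction of intervention men. Control men are offered treatment only after recurrence, and those data stay outside the trial, so non-adherence is one-sided. The analysis should use all randomised couples with outcome data, including those removed by item vi of the Protocol violation section. Missing forms leave the adherent fraction uncertain, so it should be shown over a range.
4. State the exclusion restriction: assignment acts on recurrence only through male treatment. In an open-label trial assignment could also change abstinence or condom use, and doses below the 70% cut-off may have some effect.

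The cost is a few sentences and one extra analysis. The downsides are a smaller per-protocol set, a wider interval for the complier-average estimate, and its reliance on that assumption.

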**Table 1 Tab1:**
[figure not shown]
Schedule of enrolment, intervention, assessments and specimen collection

Key: C = clinic visit - required for females only, men may complete at home, H = home procedures; AEs = adverse effects. ^a^required for females only, ^b^a slide containing vaginal secretions is collected for Nugent score; ^c^specimens added to preservative and stored for future molecular studies, ^d^male sample collection at home will be aligned with female samples

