#### Home and clinic follow up

Female participants will collect samples and complete questionnaires on four occasions after baseline including the day after completing antibiotics (day 8), and at weeks 4, 8 and 12 (Table 1, Fig. 2). At scheduled clinic visits (weeks 4 and 12) females will be assessed for BV by Amsel and Nugent criteria, and will complete a questionnaire. At day 8 and week 8, swabs, slides for Nugent scoring, and questionnaires completed at home will be returned by replied paid post to MSHC. If a woman returns a home slide with NS = 7–10, or reports symptoms indicating BV, she will be booked for an interim clinic visit and assessed for BV. All slides collected at home or in non-MSHC clinics will be sent via post to MSHC for scoring within a week. Slides with morphotypes unable to be easily scored will be read by a second independent microscopist and consensus reached.

Male participants will self-sample and complete questionnaires at enrolment and, for those in the *Intervention group*, the day after completing treatment (day 8), or if in the *Control group*, the day after their partner has finished her treatment (Fig. 2). Men will be instructed to complete their follow up specimens and questionnaires at the same time as their partner. All male questionnaires and specimens will be collected at home and returned by replied paid post to MSHC.

Validated questionnaires at each time point will collect data detailing sexual practices (e.g. frequency and types of sex, condom use, change in partnerships), contraceptive use, menstrual dates, genital symptoms, and any interim treatments. Adherence and AEs will be recorded on day 8 questionnaires and participants instructed to call the dedicated study phone if they have any enquiries or are concerned about any AEs experienced.

A reminder SMS will precede each scheduled self-collection time point and reminders sent for up to 2 weeks if samples are not returned, after which a participant will be classified as a non-responder for that interval, but contacted at the next follow-up point. A reminder SMS will be sent to participants 1–2 business days prior to any clinic-based appointment. All couples will receive a $10AUD voucher for each completed stage of follow-up.

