## Abbreviations

AE: Adverse event
BV: Bacterial vaginosis
BID: *Bis in die* (twice daily)
DSMB: Data and Safety Monitoring Board
FP: Family Planning
GP: General Practice
HIV: Human immunodeficiency virus
HREC: Human Research Ethics Committee
IUD: Intra-uterine device
mITT: Modified intention to treat
MSHC: Melbourne Sexual Health Centre
NS: Nugent score
NSW: New South Wales
PI: Principal investigator
QID: *Quarter in die* (four times daily)
RCT: Randomised controlled trial
RSP: Regular sexual partner
STI: Sexually transmitted infection
SSHC: Sydney Sexual Health Centre
TGA: Australian Therapeutic Goods Administration
TMC: Trial Management Committee
TSC: Trial Steering Committee
VM: Vaginal microbiome/microbiota

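### The stated safety summary covers only men who took a dose, so it leaves out the randomised untreated men and cannot by itself separate background symptoms from drug effects

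*Protocol article*

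**What the plan says.** **Safety population by dose.** Under Statistical methods, "all reported clinical AEs will be summarised descriptively. This will include every male who took ≥1 dose" of at least one study drug. Men in the control arm "will not receive treatment and the control for the trial is the current standard of female treatment only" (Control section), so none of them meets this definition. No comparison of adverse events between arms is stated.

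**What control men supply.** Under Home and clinic follow up, treated men complete a questionnaire the day after their own treatment ends. Control men do so "the day after their partner has finished her treatment". The questionnaires at each time point cover "contraceptive use, menstrual dates, genital symptoms, and any interim treatments", among other items, and adverse events go on the day-8 questionnaires. Neither statement is limited to one arm, and neither sets out what the control men's form contains.

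**A second rule.** Under Protocol deviation, a man who does not return the day-8 questionnaire is not eligible for the safety analysis. That rule has no dose or arm condition.

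**Deferred detail.** Statistical methods leaves the full definition of all analyses to a later statistical analysis plan.

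**The concern.** Adverse effects in men are a named additional outcome. The men receive the drugs outside approved indications (Data safety and monitoring), and the Discussion expects the result to change treatment guidelines. Guideline users need to know how many more men have symptoms because they were treated. A rate in dosed men cannot say this, because some men would have had genital or general symptoms that week without any drug.

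Randomisation supplies an untreated group of equal planned size, followed at the matching time. The stated summary leaves that group out. Choosing the population by dose is something the protocol states, so this is not simply a detail left to the analysis plan.

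**Working it through.** **1. Who is counted.** The two stated rules, side by side:

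| Man | Statistical methods | Protocol deviation |
|---|---|---|
| Dosed, day-8 form returned | in | not excluded |
| Dosed, no day-8 form | in | out |
| Control, day-8 form returned | not covered | not excluded |
| Control, no day-8 form | not covered | out |

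The rules disagree about dosed men with no form. They also leave the place of control men unclear. Non-return at day 8 is not given. If it were as high as the 15% loss assumed for week 12, it would affect 171 − 145 = 26 men per arm.

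**2. The plan's own figures.** The Sample size section gives 145 couples per arm, for 40% against 24%, two-sided 5% and 80% power. A continuity-corrected two-proportion formula returns 145. Then 290 / 0.85 = 341.2, which gives 342, or 171 per arm. These figures reproduce. They concern efficacy, and no figure is given for safety.

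**3. What a one-arm rate can tell.** All event rates below are assumptions. Let p₁ be the proportion with an event in dosed men, p₀ the proportion in control men, and n the number per arm.

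- One arm: p₁ ± 1.96 √[p₁(1 − p₁)/n]
- Excess: p₁ − p₀ ± 1.96 √[p₁(1 − p₁)/n + p₀(1 − p₀)/n]

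With n = 145 and p₁ = 20%, the one-arm result is 20% (13.5% to 26.5%) whatever the background. The excess is:

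| Background p₀ | Excess, points | 95% CI |
|---|---|---|
| 0% | 20 | 13.5 to 26.5 |
| 5% | 15 | 7.6 to 22.4 |
| 10% | 10 | 1.9 to 18.1 |
| 15% | 5 | −3.7 to 13.7 |
| 20% | 0 | −9.2 to 9.2 |

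For the 10% row: √[(0.16 + 0.09)/145] = 0.0415, and 0.10 ± 1.96 × 0.0415 = 0.019 to 0.181. The half-widths run from 6.5 to 9.2 points. The 0% row is optimistic, because the formula gives the control arm no variance there.

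**4. A second illustration.** With n = 171, p₁ = 12% and p₀ = 5%: √[(0.1056 + 0.0475)/171] = 0.0299, so the excess is 7 points (1.1 to 12.9). If the background were 2% or 10%, the same reported 12% would mean an excess of 10 or 2 points.

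**5. Precision.** At 145 per arm, power to detect a 10-point excess would be 81% at a 5% background, 67% at 10% and 50% at 20%. The comparison is therefore informative as a description but is not a powered test.

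**The case against.** **The analysis plan may already do this.** Describing events in exposed participants is standard, table layout is usually left to the analysis plan, and the protocol says who will be included without saying that control men's symptoms will not be tabulated. This stands in part: it would be too strong to say that the protocol has ruled out a comparison. But the only safety population that Statistical methods names is a one-arm one.

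**The forms may differ.** A reader might infer that both groups of men fill in the same day-8 form, so that the comparator data are certainly in hand. The documents do not support this. They show a questionnaire at the matching time, and a list of items that pools women and men. The symptom data may well allow a comparison, but this has to be confirmed.

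**Reporting is open-label and without placebo.** Treated men know that they were treated and may report more. This stands, and the difference would mix drug effect with differential reporting. The one-arm percentage has the same weakness and lacks a background rate as well.

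**The abbreviation.** Table 1 has "AEs = adverse effects" and the list of abbreviations has "AE: Adverse event". A reader might infer that only events attributed to the drug are counted. That does not follow: all reported clinical events are to be summarised, and the Trial Management Committee judges relatedness after they are reported. The mismatch is editorial.

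**Women.** A reader might also want women's events compared by arm. Both arms have the same treatment options for women, so such a table would say little about the safety of treating men.

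**Conclusion.** The point holds in a limited form. The stated safety summary is one-arm, and on its own it cannot separate background symptoms from drug effects. This is a limit of the planned summary and not necessarily of the data collected. Under an assumed 20% in dosed men, the excess is undetermined between 0 and 20 points without a comparator. With one it would be known to within about 6.5 to 9 points at 145 per arm. The documents give no event rates, so these figures only illustrate the scale. The conflict between the two safety-population rules rests on the text alone. Neither matter affects the primary efficacy analysis, but both should be settled before the data are analysed.

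**What to change.** 1. Keep the dosed-men table for adverse events and for those leading to cessation of treatment.
2. Add a descriptive table of men's day-8 symptoms by randomised arm, with risk differences and 95% confidence intervals. Include genital symptoms at least, and systemic symptoms where both forms ask the same items.
3. Confirm which items the two forms share and whether they cover the same recall period, because the form is timed from his own treatment in one arm and from his partner's in the other.
4. Make day 8 the main comparison. Under Treatment of BV recurrence, control couples may be offered male treatment after a recurrence, and those data are kept out of the trial, so later time points no longer compare treated with untreated men cleanly.
5. State one safety population, reconciling Statistical methods (every dosed man) with Protocol deviation (only men who returned the day-8 form). Say how dosed men without a form are counted.
6. State that reporting is open-label and without placebo.

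The cost is one or two extra tables and a check of the forms, with no change to design or sample size. The downside is a comparison open to differential reporting, which the caveat must make plain.
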